#### **9.3.1 Efficacy analysis set**

##### **Intention-to-treat (ITT) analysis**

the results of an experiment is based on the initial treatment assignment but not on the treatment eventually received. ITT analysis is intended to avoid various misleading artifacts that can arise in intervention research such as non-random attrition of participants from the study or crossover. ITT is also simpler than other forms of study design and analysis because it does not require observation of compliance status for units assigned to different treatments or comprise the incorporation of compliance into the analysis.

##### **Full analysis set (FAS)**

The Full analysis set will include all randomized subjects, including those who took at least 1 dose after randomization, and had at least 1 baseline and post-baseline efficacy data assessments. Subjects on FAS will be analyzed by the treatment group they were randomized to. The Full analysis set will be the primary set for efficacy analysis in the study.

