## **5.3 Packaging, labeling and storage of the investigational drugs**

### **Packaging of investigational drugs:**

Saxagliptin and vitamin D3 will all be provided in its original packaging.

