## **5.4 Compliance Evaluation**

The administration of all study drugs (including basic and investigational medication) should be recorded in the appropriate sections of the CRF.

Standard for compliant patient:  $80\% \leq \text{actual dose taken/prescribed dose} * 100\% \leq 120\%$

Standard for non-compliant patient:  $\text{actual dose taken/prescribed dose} * 100\% \leq 80\%$  or  $\text{actual dose taken/prescribed dose} * 100\% \geq 120\%$ .

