| GADA*                                       | * |   |   |   |   |   |   |   |   |   |   | * |   |   |   |   |   |   |   | * |
| Gene analysis*                              | * |   | * |   | * |   |   | * |   |   |   | * |   |   |   |   | * |   |   | * |
| Complications                   | X |   |   |   |   |   |   |   |   |   |   | X |   |   |   |   |   |   |   | X |

\*, Centralized test; 1.The contents of the discontinuation visit are consistent with that of visit 26; 2. Metformin (and insulin); 3. Saxagliptin/VitD3 (Group A does not involve any dispensation, check or retrieval of investigational medication; 4.Blood biochemical test include: Lipid (TC, LDL-C, HDL-C, and TG), liver function (AST, ALT, TBIL, DBIL, and ALB), renal function (BUN, Cr, andUA); 5.Apply to women at child-bearing period; 6.Tests for complications include: ① macroangiopathy: 1) Color Doppler Ultrasound of carotid artery, vertebral artery, and lower extremities arteries, 2) ECG; ② microangiopathy: 1) retinopathy: fundus examination and photography, 2) diabetic nephropathy: a.UACR, b. calculate eGFR; ③ peripheral neuropathy: 1) electroneuromyography, 2) physical examination using the tools in the diabetic neuropathy screening kit; ④ osteoporosis: bone mineral density. (Will accept Color Doppler Ultrasound of artery, fundus examination and photography, and electroneuromyography results from Grade A Tertiary Hospitals within 6 months prior to screening; will accept BMD test results from Grade A Tertiary Hospitals within 12 months of randomization).

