### **9.4.1 Analysis of the primary variable(s)**

The primary endpoints in the study are absolute fasting C-peptide changes between saxagliptin + metformin (and insulin) group vs. metformin (and insulin) group, and vitamin D + saxagliptin + metformin (and insulin) group vs. metformin (and insulin) group from baseline after 104 weeks of treatment. The primary endpoint will be analyzed utilizing mixed model repeated measures (MMRM) on full analysis set (FAS). Within the framework of MMRM, point estimations and 2-sided 95% CIs will be presented at each visit for the mean change within each treatment group as well as the difference of the mean change between treatment groups. The following hypothesis will be tested to establish superiority:

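### The full analysis set carries an unclear dose clause which, if applied to investigational drug, would screen only the two active arms of an open-label trial

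*Protocol*

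**What the plan says.** Section 9.3.1 of the protocol opens its FAS definition with "The Full analysis set will include all randomized subjects" and continues, in the same sentence, "including those who took at least 1 dose after randomization, and had at least 1 baseline and post-baseline efficacy data assessments". It then states "The Full analysis set will be the primary set for efficacy analysis in the study". Section 9.4.1 runs the primary mixed model for repeated measures (MMRM) on this set.

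The intention-to-treat paragraph just above says that the result of an experiment "is based on the initial treatment assignment but not on the treatment eventually received".

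On who receives what, footnote 3 to Table 1, repeated in the notes after section 6.4.15, says "Group A does not involve any dispensation, check or retrieval of investigational medication". Section 5.1 lists saxagliptin and vitamin D3 as the investigational drugs, and section 5.3 covers the same two: "Saxagliptin and vitamin D3 will all be provided in its original packaging". Group A does take the basic medication, and section 5.4 counts that among the study drugs: "The administration of all study drugs (including basic and investigational medication) should be recorded".

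Two neighbouring rules matter. Section 4.4 keeps subjects without LADA who were enrolled in error out of the FAS and allows other wrongly enrolled or randomised subjects in. Section 9.3.2 limits the safety set to patients with at least one dose of investigational product.

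**The concern.** A primary analysis set needs one rule that means the same in every arm. This sentence leaves two things open: which drug a dose refers to, and whether the clause restricts the set or merely describes part of it.

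The trial is open-label, so a decision not to start saxagliptin or vitamin D3 is made knowing the assigned arm. A control subject of the same kind has no investigational drug to refuse. If the clause is applied to investigational drug, non-starters can be removed from Groups B and C only. Both primary comparisons are against Group A, so both would then compare a selected arm with an unselected one. Randomisation no longer protects such a comparison.

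**Working it through.** **1. The plan's own sample size.** From section 9.2: means 149.2 and 108.4, so δ = 40.8; SDs 84.5 and 52.8, so σ = √((84.5² + 52.8²)/2) = 70.46; two-sided α = 0.025, so z = 2.2414; power 90%, so z = 1.2816. The protocol's formula gives

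n = 2[(2.2414 + 1.2816)/(40.8/70.46)]² + 2.2414²/4 = 74.02 + 1.26 = 75.28, rounded up to 76.

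With 20% drop-out, 76/0.8 = 95. Both stated figures reproduce, and this point does not change them.

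**2. What the FAS sentence can mean.** Planned numbers per arm (A/B/C), before the baseline and post-baseline data requirement, with x never-dosed subjects per 100 in an active arm:

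- The clause only describes, and nobody is removed for lack of a dose: 100/100/100.
- At least one dose of any study drug, basic medication counted as in section 5.4: one rule for all arms. It would remove very few subjects, because basic medication is started or adjusted from Visit 1 (section 6.4.1).
- At least one investigational dose, required where such drug is dispensed: 100/(100 − x)/(100 − x).
- At least one investigational dose, required of everyone: 0/(100 − x)/(100 − x). Neither primary comparison could be made, so this cannot be what is intended.

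**3. Which reading the text favours.** After the words about all randomised subjects, the clause adds nothing unless it restricts. The safety-set definition uses the same construction to restrict. Section 4.4 shows that the FAS is not strictly everyone randomised. The timing, after randomisation, matches how the synopsis and section 5.2 introduce saxagliptin and vitamin D3. The third reading is therefore plausible, but the text does not settle it.

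**4. Size under the third reading (illustration).** If a fraction f of an active arm is never dosed and its mean change differs from the rest of that arm by d, removing it moves the arm mean by f × d. The protocol gives neither f nor d. Taking d as the planned difference:

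- f = 0.05: 0.05 × 40.8 = 2.04 pmol/L, which is 5% of 40.8.
- f = 0.10: 0.10 × 40.8 = 4.08 pmol/L, which is 10% of 40.8.

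Only never-dosed subjects who give a post-baseline C-peptide count towards f. Section 7.1 schedules the first such sample at Visit 8 (week 26), and section 6.6 asks for the Visit 26 assessments at discontinuation.

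**5. Power if non-starters are excluded.** With 100 per arm and 20% drop-out, 80 are evaluable in Group A and 80 × (1 − x/100) in the active arm. Power = Φ(40.8/(70.46 × √(1/80 + 1/n_active)) − 2.2414):

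- x = 0, n_active = 80: 92.2%
- x = 5, n_active = 76: 91.5%
- x = 10, n_active = 72: 90.7%

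**6. Dilution if non-starters are kept.** Suppose they change as controls do while starters gain the full 40.8. The difference becomes 40.8 − 2.04 = 38.76 at 5%, or 40.8 − 4.08 = 36.72 at 10%. With 80 evaluable per arm the standard error is 70.46 × √(2/80) = 11.14. Power is then Φ(38.76/11.14 − 2.2414) = 89.2% or Φ(36.72/11.14 − 2.2414) = 85.4%.

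**The case against.** The strongest reply is that the sentence begins with all randomised subjects, that the word joining the two halves includes rather than excludes, and that no drug is named. Section 5.4 counts metformin and insulin as study drugs, so a common rule met in all three arms is available. The protocol also names the investigational product when it means it, as in section 9.3.2, and it analyses FAS subjects in the arm to which they were randomised. The non-starter rates have no source in the protocol. A never-dosed subject without a later C-peptide adds no outcome to the MMRM, whatever the clause says. A statistical analysis plan could settle which dose is meant.

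Much of this stands. A reader might infer that the sentence removes the whole control arm, or that Group A receives no study drug. The documents support neither: the text does not tie the dose to investigational product, and Group A takes basic medication. The explicit investigational-dose rule belongs to the safety set. Read with section 5.1, that rule would leave Group A out, although the synopsis places the basic medication under a heading that names the investigational product, so even there the term is not used consistently.

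What does not stand is leaving the matter to a later document. The protocol already defines the primary set, and section 9.1 requires the analysis plan only before database lock. In an open-label trial, the reading could then be chosen after arm-level data have been seen.

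**Conclusion.** The point holds as a drafting fault in the primary analysis set. The clause is ambiguous about the drug and about whether it is a condition, and one plausible reading screens Groups B and C but not Group A. That reading conflicts with the intention-to-treat paragraph. On the descriptive reading there is no conflict, and the same is nearly true if any study drug counts.

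Neither the size nor the direction of bias can be known from the protocol. The 2-4 pmol/L shift assumes 5-10% never dosed but still sampled, and a 40.8 pmol/L difference between them and the rest of the arm. A lower rate or a smaller difference reduces it in proportion. The loss of power from exclusion is at most 1.5 percentage points in these scenarios (92.2% to 90.7%), so the issue is selection, not precision. The correction is worth making because it is cheap and removes a discretionary choice from the analysis that decides the trial.

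**What to change.** In section 9.3.1, define the FAS as all randomised subjects, analysed in the arm to which they were randomised, with no dose condition. Say in the same place how this fits with the section 4.4 exclusion of subjects without LADA enrolled in error. The MMRM then uses every subject with a post-baseline C-peptide, dosed or not.

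In the same edit, reword section 9.3.2 so that the safety set includes Group A, for example by an entry rule that can be met equally in all three arms.

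The cost is a change of wording in two definitions and some dilution by non-starters. Under the pessimistic assumption that they gain nothing, the estimate falls by 2-4 pmol/L and power goes from 92.2% to about 89% at 5% non-starters, or 85% at 10%. With fewer non-starters who return for sampling, the cost is smaller. An analysis restricted to subjects who started treatment can still be reported as supportive.

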##### **Per protocol (PP) analysis set**

The PP analysis set is a subset of the Full analysis set that includes subjects who do not have significant protocol deviations that affect the study outcome. These exclusions from the PP analysis set will include but not be limited to the patients who took prohibited concomitant medications and major protocol deviations or violations. The exclusions from the PP analysis set will be determined prior to database lock on data review meeting.

### **9.3.2 Safety analysis set**

Safety analysis Set (SS) is a subset of all patients enrolled set including patients who take at least one Investigational Product (IP) dose and have any safety records that can be found in the study database. Analysis will only use values that are actually measured.

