The U.S. medicine institute of food and nutrition committee concluded some study evidence from vitamin D which covers different dose range (800 – 300000 IU/day) and duration (a few months to years). Vitamin D supplement < 10000IU/day scarcely lead to poisoning. However, undiagnosed primary hyperparathyroidism patients can be found when given vitamin D treatment. Genetic abnormal metabolism or other comorbidities like chronic kidney disease, granuloma or hyperparathyroidism, can make the patients susceptible to vitamin D supplementation. There is no clear evidence showing the relation between the upper safety level of 25(OH)D and hypercalcemia. Most experts believed that when 25(OH)D<150 nmol/L, generally there is no need to worry about the side effects of vitamin D . The results from studies about vitamin D dose response differ from study to study. Among these studies, the UV exposure in summer is the important confounding factor.

The current evidence is not sufficient on the time to monitor the response to vitamin D treatment,. According to the pharmacokinetics of 25(OH)D, it should be monitored within 1 month of the final full load. Most studies have shown that 25(OH)D can reach a new steady state after about 3 months, but some studies have found that 25(OH)D has not reached steady state levels in 6 months after treatment. Therefore, some experts believe that one month after the vitamin D load supplementation, or after vitamin D supplementation, symptoms of subclinical primary hyperparathyroidism is revealed, and serum calcium should be corrected. There is no need to routinely measure 25(OH)D, which can result in wasted resources. However, considering that the dose of vitamin D used in this study is 2000 IU/day, exceeding the upper limit of 800 IU/day specified by the specification, researchers, ethics committee members and subjects will be very concerned about the safety of treatment; Different people have different sensitivities to vitamin D treatment, and some people may have increased sensitivity, which may increase the risk of poisoning or adverse reactions; and only one of the three groups received vitamin D. Is there a difference in the safety of the treatment among three groups? Is this difference related to different vitamin D levels? Regular measurements of 25(OH)D are needed to answer these questions.

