### **7.2.1 Laboratory tests**

The sponsor will assign the central laboratory to carry out the safety assessment: test of 25(OH)D. Other clinical lab tests will be carried out at laboratories of each research center.

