### **9.3 Definitions of analysis sets**

The primary efficacy analysis population will be based on the Full Analysis Set (FAS) and the Per-Protocol Analysis Set (PP). The secondary analysis population and the safety analysis population will be based on the Per-Protocol Analysis Set (PP) and Safety Analysis Set (SS), respectively.

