#### **9.4.3 Analysis method for safety endpoints:**

The incidence of adverse events (AEs) and apparent abnormal central laboratory results will be summarized according to different treatment groups. All severe adverse events and AEs that cause discontinuation from the study will be recorded in detail. All changes of clinical laboratory parameters and vital signs at each scheduled time points from the baseline will be summarized according to treatment groups.

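### Read literally, the safety set requires an investigational product dose that the control arm never receives, so it contains no metformin (and insulin) comparator

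*Protocol*

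**What the plan says.** Section 9.3 assigns the populations: "the safety analysis population will be based on the Per-Protocol Analysis Set (PP) and Safety Analysis Set (SS), respectively". Safety is therefore analysed on the safety set, which section 9.3.2 defines: "Safety analysis Set (SS) is a subset of all patients enrolled set including patients who take at least one Investigational Product (IP) dose". The only other condition is that the patient has some safety record.

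Section 5.1 lists the investigational products in a table of two rows, saxagliptin and vitamin D3. Section 5.2 places metformin and insulin under basic medication and the other two drugs under investigational medication. Section 5.4 keeps the same split for compliance. Footnote 3 to Table 1, repeated after the Visit 26 schedule, says: "Group A does not involve any dispensation, check or retrieval of investigational medication".

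The protocol nevertheless wants safety by arm. The benefit/risk section asks: "Is there a difference in the safety of the treatment among three groups". In section 9.4.3, the incidence of adverse events and "apparent abnormal central laboratory results will be summarized according to different treatment groups". On where tests are done, section 7.2.1 assigns 25(OH)D to the central laboratory and adds: "Other clinical lab tests will be carried out at laboratories of each research center".

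**The concern.** The entry rule for the safety set is written in terms of a drug class that one of the three arms does not take. A programmer who applies the definition would build a safety set with no control patients.

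The safety objective gives particular weight to severe hypoglycaemia and hypercalcaemia. Every arm may use insulin, and the benefit/risk section names hypoglycaemia as the main concern with insulin. A hypoglycaemia rate under saxagliptin therefore cannot be interpreted without the rate under metformin (and insulin) alone. Without Group A, no excess can be attributed to saxagliptin, nor to saxagliptin and vitamin D3 together.

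The second, smaller issue is that the incidence summary of abnormal laboratory results in section 9.4.3 is worded for a laboratory that performs only one of the safety tests.

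**Working it through.** **Planned arm sizes.** These rest on the sample size in section 9.2, so that figure is checked first. The inputs are means 149.2 and 108.4 (difference 40.8), SDs 84.5 and 52.8, two-sided α = 0.025 and power 90%.

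- σ = √[(84.5² + 52.8²)/2] = 70.46
- z for two-sided 0.025 = 2.2414; z for 90% power = 1.2816
- n = 2[(2.2414 + 1.2816) × 70.46/40.8]² + 2.2414²/4 = 75.28, rounded up to 76, as stated
- With 20% drop-out: 76/0.80 = 95, as stated, then set to 100 per group and 300 in total

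The sample size reproduces and is not affected by this point. The planned arms are 100/100/100.

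**Who meets the section 9.3.2 rule.** This is a count, not a power calculation. The figures are maxima, because a patient must also take a dose and have a safety record.

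| Arm | Investigational product under section 5.1 | Maximum in safety set as written | Maximum if any regimen component counts |
|---|---|---|---|
| Metformin (and insulin), Group A | none | 0 | 100 |
| + saxagliptin | saxagliptin | 100 | 100 |
| + saxagliptin + vitamin D3 | both | 100 | 100 |
| Total | | 200 (67% of 300) | 300 |

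**Which comparisons remain under the literal rule.**

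- Saxagliptin versus control: lost.
- Saxagliptin plus vitamin D3 versus control: lost.
- Saxagliptin plus vitamin D3 versus saxagliptin: kept, 100 versus 100. These two arms differ by design only in vitamin D3.

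**Laboratory wording.** Section 7.2.1 gives 25(OH)D as the only central safety test. Its table of tests done at each centre includes calcium, creatinine, AST, ALT and bilirubin. The incidence sentence in section 9.4.3 therefore reaches 25(OH)D alone. Two other provisions cover part of the gap:

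- The last sentence of section 9.4.3 summarises changes from baseline in all clinical laboratory parameters by group, without restriction to the central laboratory.
- Section 8.1.1 makes a clinically meaningful abnormality an adverse event, and adverse events are tabulated by group.

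What remains uncounted is the incidence of local abnormalities that do not qualify as adverse events. Calcium shows why this matters. Section 8.6 suspends vitamin D3 when hypercalcaemia is confirmed, and under section 8.1.1 a change in dosing makes the finding an adverse event. That route exists only in the vitamin D3 arm. A mild, asymptomatic rise in another arm need not become an adverse event, so a count that relies on adverse events alone may not be comparable across arms.

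**The case against.** The strongest reply is that the protocol does not use the term consistently. The synopsis section headed with investigational product, dosage and administration opens with metformin and insulin, and the Table 1 footnote speaks of investigational medication rather than product. On that usage Group A does take investigational product. This does not rescue the rule. The synopsis goes on to list saxagliptin and vitamin D3 alone under their own investigational heading, and sections 5.1, 5.2 and 5.4 keep the classes apart. The word *including* in section 9.3.2 could be read as non-exclusive, but the sentence defines a subset and gives no other way in.

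A second reply is that the intent is plain. Adverse events are recorded from consent for every patient, the visit schedule gives all arms the same safety tests, and section 9.4.3 reports by treatment group. That stands. It makes this a drafting error, and it does not show that the sponsor means to drop Group A. An SAP could restore the arm, but only by contradicting the definition that the protocol fixes.

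Three stronger readings are tempting and are not supported:

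- *No excess could be attributed to vitamin D3 either.* The comparison of the two saxagliptin arms isolates vitamin D3, including for hypercalcaemia, and both arms meet the literal rule.
- *The full analysis set has the same fault.* Its phrase, "including those who took at least 1 dose after randomization", names no drug. Metformin taken as assigned can satisfy it in Group A.
- *Abnormal calcium goes unreported.* Changes from baseline are summarised by group, and clinically meaningful abnormalities are adverse events. Only the incidence count of the remaining local abnormalities is missing.

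**Conclusion.** The definition in section 9.3.2 is wrong as written and should be corrected. Taken literally, it admits 0 of 100 control patients and at most 200 of 300 overall. This conflicts with section 9.4.3 and with the three-group safety question in the benefit/risk section. Both comparisons with metformin (and insulin) are lost, and the vitamin D3 comparison within saxagliptin-treated patients is kept. No data are lost and no primary efficacy inference depends on this set.

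The conclusion assumes that investigational product carries its section 5.1 meaning, that arms reach the planned 100, and that Group A is the metformin (and insulin) arm, the only arm for which the footnote can hold. The SAP was not available.

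The laboratory wording in section 9.4.3 is a secondary point, limited to the incidence of local abnormalities that are not adverse events.

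**What to change.** In section 9.3.2, define the safety set as all randomised patients who took at least one dose of any component of their assigned regimen after randomisation and have any safety record. State that basic medication satisfies this condition for Group A.

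In section 9.4.3, extend the incidence summary of abnormal results to central and local laboratory results, by treatment group.

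The cost is a few words in two sections. Adverse events, medication records and local laboratory results are already collected in all three arms, so there is no new data collection and no effect on the sample size. Because the trial is open-label, the change is best made and dated before data by arm are reviewed, and carried into the SAP.
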